# Efficacy and safety of Myofascial-meridian Release Acupuncture (MMRA) for chronic neck pain: a study protocol for randomized, patient- and assessor-blinded, sham controlled trial

**DOI:** 10.1186/s12906-016-1027-y

**Published:** 2016-02-02

**Keywords:** Chronic neck pain, Myofascial-meridian release acupuncture, Randomized controlled trial

## Abstract

**Background:**

The purpose of this study is to evaluate the efficacy and safety of myofascial-meridian release acupuncture (MMRA) in the treatment of chronic neck pain compared with sham acupuncture.

**Methods/design:**

A protocol for a randomized, patient- and assessor-blinded, sham controlled parallel trial is presented. Seventy-four participants with a ≥3 month history of neck pain and a score of ≥4 on the 11-point pain intensity numerical rating scale (PI-NRS) will be randomly assigned to the MMRA group (*n* = 37) or sham acupuncture group (*n* = 37). The participants will receive the MMRA treatment or sham acupuncture treatment twice per week for 4 weeks. The primary outcome is the mean change in the PI-NRS (0 = no pain and 10 = worst possible pain, 11-point Likert scale) from baseline to 4 weeks. The secondary outcomes are the mean change from baseline on the clinical relevance of the pain (ratio of changes greater than 1.5 or with percentiles greater than 30 % and 50 % in the PI-NRS), function (Neck Disability Index and Cervical Range of Motion), autonomic and psychometric measurements (Heart Rate Variability and Perceived Stress Scale), quality of life (EuroQol), global assessment (Patient Global Impression of Change), semi-objective outcomes (pressure pain threshold, consumption of rescue medicine and days of restricted activity) and immunologic/stress biomarkers. Adverse events will be evaluated at every visit.

**Discussion:**

The results of this trial will provide evidence to confirm the efficacy and safety of acupuncture for chronic neck pain.

**Trial registration:**

The trial is registered with the Clinical Research Information Service (CRiS), Republic of Korea: KCT0001573.

## Background

Neck pain is one of the most common symptoms in patients suffering from musculoskeletal pain [1, 2]. More than 70 % of adults in the general population suffer from neck pain at some point throughout their life [2, 3]. The Neck Pain Task Force reported that the 1-year prevalence of neck pain ranges from 30 to 50 % in the general population, and 2 to 11 % of these patients report restricted daily activities [4]. Neck pain is also common in most occupational groups, and 11 to 14 % of workers are restricted in their activities [4]. Not only daily life activities are diminished in chronic neck pain patients but also health-related quality of life (HRQoL). In a cross-sectional study, HRQoL was negatively correlated with prevalent neck pain [5], and the existence of neck pain was also a predictor of poor future physical HRQoL in a longitudinal study [6].

There are several modifiable risk factors, such as exposure to tobacco from direct smoking, physical activity, psychologic health and repetitive and sedentary work positions [4]. Otherwise, the pathophysiological pathway of chronic neck pain is not well established. However, there are several previous studies on the relationship between neck pain and inflammation or stress. In a human study, elevated inflammation associated chemotactic cytokines, such as IL-1β, IL-6, CRP and tumor necrosis factor-α (TNF-α), were suggested to be contributors to musculoskeletal disorders [7]. In cross-sectional results for patients with neck, shoulder and back pain, cortisol was found to be a stress biomarker and was significantly higher in the “pain” groups than in the “no pain” group [8].

Many trials have been conducted to evaluate the effect of acupuncture on chronic neck pain. However, several limitations have hindered conclusions on the value of acupuncture for chronic neck pain. First, according to a recent systematic review, many acupuncture chronic neck pain studies report subjective outcomes related to pain and disability using tools such as the visual analogue scale (VAS) and the Neck Disability Index (NDI) [9]. However, the placebo treatment had higher clinical effects than no treatment when measured by a subjective continuous outcome variable [10]. Moreover, in pain treatment, subjective outcomes cannot avoid the risk of bias [11]. Second, while there are several reviews on the effectiveness of acupuncture in chronic neck pain, no accepted mechanism is known; though, the chronic neck pain might be related with immunologic or stress factors. A lack of biological plausibility is also one of the problems of acupuncture studies about pain [12]. Third, although a minimal clinical important difference (MCID) is important in interpreting the clinical relevance of trial results, almost no trial about acupuncture for chronic neck pain considered the MCID when designing and interpreting the clinical trials. Finally, in many acupuncture trials, the treatment protocol is different from daily medical practice. Therefore, the results do not correlate well with applied clinical practice.

In view of the limitations of previous studies, our study outlines several improvements. First, we adapted a Park sham device (PSD; Acuprime, Exeter, UK) that is a widely used, validated sham device in acupuncture research [13] to evaluate the efficacy of acupuncture treatment in chronic neck pain with semi-objective outcomes, such as the pressure pain threshold, consumption of rescue medication and days of restricted activity. Second, we will explore the mechanism of acupuncture treatment in chronic neck pain and if the efficacy is mediated by inflammation and stress reduction. Third, to evaluate the clinical relevance and statistical significance, the MCID will be used to design a research protocol and interpret the results of the trial. Finally, we will reflect clinical practice by applying the myofascial-meridian release acupuncture (MMRA) treatment protocol that is used at the Spine and Joint Clinical Center in Kyung Hee University Korean Medicine Hospital, which will increase the external validity.

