### Outcome measurement

The detailed outcome measurement time points are provided in Table 1.

**Table 1 Tab1:** Schedule for the treatment and outcome measurements

Visit	S	1	2	3	4	5	6	7	8
Week		1		2			3	4	
Informed consent	●								
Demographic characteristics	●								
Vital signs	●	●	●	●	●	●	●	●	●
Blood test	●								●
Medical history	●								
Inclusion/Exclusion criteria	●								
Conformity assessment	●								
Treatment expectancy questionnaire	●								
Random allocation		●							
Treatment		●	●	●	●	●	●	●	●
Prescription of rescue medicine		●							
PI-NRS		●	●	●	●	●	●	●	●
NDI		●							●
CROM		●							●
HRV		●							●
Perceived stress scale		●							●
EQ-5D		●							●
PGIC									●
Pressure pain threshold		●							●
Consumption of rescue medicine									●
Days of restricted activity		●							●
Blinding test		●							●
Safety assessment		●	●	●	●	●	●	●	●

Visit 1: within 4 weeks after screening, Visit 8: 4 weeks after Visit 1 (+6 days)

*CROM* Cervical Range of Motion, *NDI* Neck Disability Index; *PGIC* Patient Global Impression of Change, *PI-NRS* 11-point Pain Intensity Numerical Rating Scale, *S* screening visit

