#### Primary endpoint

The primary outcome is the mean change in the PI-NRS (0 = no pain and 10 = worst possible pain, 11-point Likert scale) from the baseline to 4 weeks. The PI-NRS has been widely used to assess chronic pain intensity in conditions such as chronic low back pain, fibromyalgia, osteoarthritis, diabetic neuropathy and post-herpetic neuralgia in placebo-controlled clinical trials [24]. In a previous study, the minimal clinically important change of PI-NRS score was 1.5 points in chronic neck pain patients [25]. Compared with global assessments of change in pain perception, the clinically important differences were a 30 % reduction of PI-NRS as “much improved” and a 50 % reduction of PI-NRS score as “very much improved,” regardless of disease, gender, age, study result or treatment group [24]. The participants will be instructed not to take a rescue medicine 4 h before assessing the pain intensity.

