##### Autonomic and psychometric measurement

The mean change from baseline for autonomic and psychometric measurements will be assessed by heart rate variability (HRV) and perceived stress scale (PSS). HRV will be evaluated by the commercial device PowerLab Biomap ML132 (AD Instrument, Castle Hill, Australia) with a 400 Hz sampling rate. HRV measurements will be conducted according to the guidelines written by the task force of the European Society of Cardiology and the North American Society of Pacing and Electrophysiology [29]. The standard deviation (SD) of the NN interval, square root of the mean squared differences of successive NN intervals, Low frequency (LF), High frequency (HF), LF/HF ratio and Total Power will be evaluated. Developed in 1983 by Cohen [30], the PSS is a self-reported questionnaire that evaluates degree of the individual’s perceived stress with a 5 point-Likert scale consisting of 14 questions. The questionnaire was translated into Korean, and the reliability and validity of the Korean version of the PSS [31] was studied.

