##### Biomarkers

Inflammatory/immunologic and stress biomarkers will be assessed at 1 and 4 weeks after randomization. Biomarkers of inflammation such as ESR and CRP; immunologic markers such as IL-1B, IL-6, TNF-α, IFN-γ; and stress markers such as serum cortisol were chosen according to previous research [36, 37]. Blood samples were collected from 10:00 to 11:30 am to minimalize the cortisol changes throughout the day.

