Specifically, we will focus on the mechanism of the acupuncture treatment in chronic neck pain. Biomarkers of inflammation, such as IL-1β, IL-6, CRP and TNF- α, are known to be related to musculoskeletal pain [7, 36, 37]. Several animal studies showed that acupuncture stimulation changed cytokine levels by endogenous opioid and non-opioid means [42]. Electroacupuncture treatments are also known to reduce pro-inflammatory cytokines in peripheral lesions and the spinal cord [43]. Recently, electroacupuncture has been suggested to have an anti-inflammatory effect and affect the production of catecholamines in the adrenal glands by mediating the sciatic and vagus nerves [44]. Various stress variables, such as cortisol level, a stress questionnaire and HRV, are also likely to be correlated with neck pain [8, 45–48]. In an acupuncture trial in knee osteoarthritis, 10 days of an electroacupuncture treatment resulted in a significant improvement in objective measures of stress-associated biomarkers, such as plasma cortisol, as well as subjective measures, such as pain, stiffness and disability. In another acupuncture trial in chronic fatigue syndrome, 10 sessions of acupuncture treatment for 4 weeks reduced the stress measured by a Stress Response Inventory questionnaire. In a pilot study with night-shift-working nurses, acupuncture treatment attenuated the imbalance between sympathetic and parasympathetic activities measured by HRV [49]. However, whether acupuncture treatment reduces chronic neck pain through inflammation and stress levels is not clear. In this study, we will conduct an exploratory data analysis to elucidate the role of MMRA treatment in managing inflammation and stress levels in chronic neck pain patients to determine if acupuncture is associated with physiological changes beyond the placebo effects.

To summarize, our protocol adopted several improvements to overcome the limitations of previous chronic neck pain acupuncture research while considering the clinical relevance and determining a mechanism of acupuncture treatment.

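### The follow-up PSS and HRV values fall at the same visit as the primary pain score, so the exploratory question of mediation by stress reduction cannot be answered as scheduled; for blood markers the same holds on Table 1

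*Protocol article*

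**What the plan says.** The Background lists four improvements over earlier acupuncture trials. The second is to explore how acupuncture works in chronic neck pain and "if the efficacy is mediated by inflammation and stress reduction". The Discussion returns to this: "we will conduct an exploratory data analysis to elucidate the role of MMRA treatment in managing inflammation and stress levels". It then sums up the protocol as overcoming earlier limitations "while considering the clinical relevance and determining a mechanism of acupuncture treatment".

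Table 1 (Outcome measurement) sets the timing:

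- The row "Perceived stress scale" and the HRV row are marked at Visits 1 and 8 only.
- The blood-test row is marked at screening and Visit 8 only.
- The PI-NRS row is marked at all eight visits. The primary endpoint is its change from baseline to week 4, which is Visit 8 according to the table footnote.

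The Biomarkers section differs from the table: "Inflammatory/immunologic and stress biomarkers will be assessed at 1 and 4 weeks after randomization".

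The Objective section lists the autonomic, psychometric and biomarker measures only as comparisons with sham.

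**The concern.** Mediation is a claim about order: treatment changes stress or inflammation, and that change then lowers pain. To support it, the mediator has to be seen after treatment begins and before the pain outcome. Under Table 1 its only follow-up value comes at the outcome visit. Pain, by contrast, is recorded throughout the course, so pain change is observed before the mediator's follow-up value. For a stress questionnaire the reverse path, in which people feel less stressed because their neck hurts less, is highly plausible.

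Randomization protects the comparison of arms on pain and the comparison of arms on stress. It does not give a direction to the link between the two. A later analysis plan cannot supply a time order that was never measured. At stake is a mechanism claim that the article presents as an advance on earlier trials: a treatment acting on pain alone could appear to act through stress.

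**Working it through.** **1. Timing, side by side (Table 1 and the Biomarkers section)**

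| Measure | Baseline | Between start of treatment and Visit 8 | Visit 8 |
|---|---|---|---|
| PI-NRS | Visit 1 | Visits 2 to 7 | yes (primary) |
| PSS | Visit 1 | none | yes |
| HRV | Visit 1 | none | yes |
| Blood test, Table 1 | screening | none | yes |
| Biomarkers, text | unclear | week 1, if read literally | week 4 |

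Table 1 labels Visit 1, the randomization visit, as week 1 and shows no blood draw between screening and Visit 8. The text's first time point therefore probably means the baseline sample. Even on the literal reading, only the blood markers would gain an earlier value.

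**2. The plan's own inputs (Sample size calculation)**

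Difference 1.5; SDs of change 1.88 and 2.21; two-sided 5 %; power 80 %.

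SD = √[(1.88² + 2.21²)/2] = √[(3.5344 + 4.8841)/2] = 2.05, so d = 1.5/2.05 = 0.731.

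The noncentral t gives power of 79.5 % with 30 per group and 80.8 % with 31. Then 31/0.85 = 36.5, rounded up to 37 per arm and 74 in total. The stated sample size reproduces.

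**3. What concurrent measurement does if stress only follows pain**

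Model: pain change Y = cT + e, with T the arm and c = 1.5. Mediator change M = kY + u, with no effect of M on Y. Let r be the within-arm correlation of Y and M. The documents give no value for r, so a range is assumed.

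- Path a (arm to mediator) = kc.
- Path b (mediator to pain, given arm) = k·var(e)/[k²·var(e) + var(u)].
- Apparent proportion mediated = ab/c = k²·var(e)/[k²·var(e) + var(u)] = r².

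A joint-significance test declares mediation when both paths have p < 0.05. With 31 per arm:

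- Path a has standardized effect 0.731r and noncentrality 0.731r·√(31/2), on 60 df.
- Path b has noncentrality approximately r/√(1 − r²)·√59, on 59 df.

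| Assumed r | Power, path a | Power, path b | Product | Simulated (4000 trials) | r² |
|---|---|---|---|---|---|
| 0 | 5 % | 5 % | 0.25 % | 0.1 % | 0 % |
| 0.2 | 8.8 % | 33.8 % | 3.0 % | 2.9 % | 4 % |
| 0.3 | 13.6 % | 66.1 % | 9.0 % | 9.6 % | 9 % |
| 0.5 | 29.4 % | 99.2 % | 29 % | 30 % | 25 % |
| 0.7 | 50.9 % | 100 % | 51 % | 51 % | 49 % |

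Other simulation runs of the same model gave 8 % at r = 0.3, and 28–30 % and 50–52 % at r = 0.5 and 0.7.

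**4. Does a mid-course PSS help?**

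The reverse-path model was kept, with the PSS taken mid-course and the mediator-to-pain path adjusted for PI-NRS at that same visit. Assumed: half the effect (0.75) present by then, and a within-arm correlation of 0.6 between mid-course and final pain. False mediation was 0.5 %, 0.6 % and 1.0 % (rounded) at r = 0.3, 0.5 and 0.7. This treats PI-NRS as capturing the pain that drives stress; error in PI-NRS would leave some residual bias.

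**The case against.** The strongest reply is that mediation is not a formal objective. The Objective section asks only for comparisons with sham, and measurement at Visits 1 and 8 serves that. The Statistical analysis section gives two-group tests for secondary endpoints and names no mediation test. The Discussion calls the mechanism work exploratory and, in the same sentence, asks whether acupuncture goes along with physiological change beyond placebo, which is a question of association. All of this stands. It narrows the problem to the Background clause and the Discussion's closing phrase, both of which promise more than the schedule can deliver. It does not remove the mismatch, because an exploratory analysis should still be able to address its own question.

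Two stronger readings are tempting and are not supported:

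- A reader might infer that no candidate mediator at all is measured between the start of treatment and the outcome. That is firm for PSS and HRV. For blood markers it depends on preferring Table 1 to a literal reading of the Biomarkers section.
- A reader might take false-mediation rates of 30 % or 50 % as typical of this trial. Nothing in the documents supports correlations of 0.5 to 0.7, least of all for cytokines, CRP, ESR, cortisol or HRV. At r = 0.2 the rate is about 3 %.

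It is also fair to say that the number of mediator time points an exploratory aim deserves in a 74-person trial is partly a matter of preference.

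**Conclusion.** The point holds in limited form. For PSS and HRV the schedule cannot separate stress reduction lowering pain from pain relief lowering stress. For blood markers the same is true on Table 1, subject to reconciling it with the Biomarkers section. The false-mediation rates illustrate the consequence and do not predict it: they rest on an assumed correlation, a pure reverse-path model, 31 completers per arm and a test that the protocol does not specify. The primary comparison, the sample size, the randomization and all between-arm comparisons of secondary outcomes are unaffected. Severity is minor: worth considering because the remedy is cheap and changes what the mechanism work can conclude.

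**What to change.** 1. Add the PSS at one existing mid-course visit (Visit 4 or 5), completed before that day's session. Analyse its change from baseline as mediator of the later PI-NRS change, adjusting for baseline PSS, baseline PI-NRS and PI-NRS at that same mid-course visit. Add HRV there too if the device is available.
2. For blood markers, and for HRV if it is not added, reword the Background and the end of the Discussion. State the aim as between-arm differences and association with pain change, with no claim of mediation or of settling a mechanism.
3. Reconcile the Biomarkers section with the blood-test row of Table 1.

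The cost is a few minutes of participant time at one visit and a more modest mechanism claim. No extra blood draw or visit is needed, and the sample size does not change. The added PSS restores time order only for perceived stress. It does not remove unmeasured common causes of stress and pain, so the result should still be reported as exploratory.

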## Methods/design

### Objective

The aims of this study are to assess the efficacy and safety of MMRM in treating chronic neck pain for pain intensity, function, autonomic and psychometric measurements, quality of life, global assessment, biomarkers and adverse events compared with sham acupuncture.

### Design and setting

This study is an equal randomized, stratified (11-point pain intensity numerical rating scale (PI-NRS) score ranging from 4 to 6 in one group and 7 to 10 in one group), patient- and assessor-blinded, sham controlled, parallel-group, single center, clinical trial conducted in Korea.

#### Recruitment period

The participants will be recruited from the Kyung Hee University Korean Medicine Hospital in Seoul, which has a population of approximately 10,078,000. Recruitment is expected from August 2015 to April 2016.

#### Methods of recruitment

A total of 74 participants with chronic neck pain will be recruited from the outpatients of Kyung Hee University Korean Medicine Hospital. We will recruit the participants by advertising on the hospital homepage and bulletin board, in the media (local newspapers and public newsletters) and on the internet homepages of public institutions.

#### Study plan

After oral and written consent is obtained from each patient, subject information will be collected at the first visit. After a participant voluntarily consents to the study, they will be screened using inclusion/exclusion criteria at the first visit. If the participants take the pain medications, a ten-day wash-out period will be needed. At the end of the screening phase, if an eligible participant meets the study criteria with moderate (PI-NRS score range from 4 to 6) or severe (PI-NRS score range from 7 to 10) chronic neck pain, then the subject will be randomly allocated into 1 of 2 groups (the MMRA or sham acupuncture group) with a 1:1 allocation ratio. The MMRA group and sham acupuncture group will receive a total of 8 acupuncture treatment sessions during 4 weeks. MMRA acupuncture will be conducted at traditional acupuncture points, or ashi points, with deqi sensation. Sham acupuncture will be performed at non-acupuncture points without deqi sensation using a PSD. After a 4-week treatment, primary outcome measurements will be evaluated.

### Types of participants

#### Inclusion criteria

Participants who meet the following conditions will be included: (1) Males and females aged 19 to 75 years; (2) Suffering from neck pain for at least 3 months (Neck pain is defined as pain and stiffness around the cervical spine that can be aggravated with movement or pressure.); (3) Classified as Grade I, II (no radiculopathy or structural pathology) according to The Bone and Joint Decade (2000–2010) Task Force on Neck Pain; (4) A score more than 4 on PI-NRS at the time of recruitment; (5) Agreement via written informed consent after being provided with an explanation regarding the purpose and characteristics of this study.

#### Exclusion criteria

Participants who have experienced or have one or more of the following conditions will be excluded: (1) radiating pain or upper limb symptoms at areas excluding the neck (scapula included); (2) Neurological abnormalities such as decreased deep tendon reflexes, weakness and/or sensory deficits; (3) Signs or symptoms from major structural pathology such as fracture, myelopathy, neoplasm or systemic diseases; (4) History of surgery or other congenital abnormalities of the cervical spine; (5) Receiving treatment for psychiatric conditions, such as epilepsy, depressive disorder or panic disorder; (6) Suffering from pain in another area that is greater than the neck pain; (7) Received acupuncture, medication, physical therapy or manipulation therapy for neck pain within the last 2 weeks; (8) Known hypersensitive reaction after acupuncture treatment or an inability to cooperate with the acupuncture procedure; (9) Pregnant, breast-feeding or expecting a pregnancy during the study period; (10) Other factors that have been deemed inadequate for participation by research investigators.

